**2.2.6 Primary endpoint**

Coronary Stent Healing Index (cumulated):

1. Uncovered struts: 2% =1 – 5% =2 – 10% =3 - 15% =4 – 20% =5 – 25% =6 – 30% =7 – 35% =8 – 40% =9

2)    Uncovered struts in fornt of side branch on acquired or persistent malapposed struts. 10% =1 – 20% =2 – 30% =3 etc… til 100%=10

3)     Persistent malapposition: ≥2 nabo struts længde mindst 1 mm =1 ; ≥2mm=3 ; ≥3 mm = 3

4)     Acquired malapposition: ≥2 adjacent struts of at least 1 mm length  =2 ; ≥2mm=4 ; ≥3 mm = 6

5)     Neointimal thickness in one frame >200 =1 - >300 =2  - >400 =3 or diameter stenosis >50% =4 - > 75% =5

6)      Cumulated extra stent lumen increase in match cross sectional analysis: (gns. areal mål): ≥0.2mm2 =1 ; ≥0.4 mm2 = 2; ≥0.6mm2=3 ; ≥0.8 mm2 = 4 ;  ≥1.0 mm2=5 ; ≥1.2 mm2 = 6

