### OPTIS St. Jude Medical OCT system will be used. Pre PCI: (after predilatation) OCT imaging catheters will be inserted and advanced to a position distal to the lesion and acquisition of the lesion will be performed at 36 mm/s (OPTIS). Final result acquisition: the OCT imaging catheters will be inserted and advanced to a position with acquisition start at least 5 mm distal to the distal stent edge. Pullback speed 20 mm/sec covering the. If target segment is longer than 53 mm then an additional pullback is performed covering entire target area. Final result is acquired by OCT. Flushing is performed by automated injector or manual injection. Iomerone contrast will be used for flushing. In case of difficult flushing, a larger guiding catheter or a more co-axial position of the guiding catheter is recommended. OCT files from baseline, follow-up and events (pre-intervention) should be submitted in RAW format to the Interventional Imaging Core Laboratory at Aarhus University Hospital via the study organization. Flushing for 3 seconds of the OCT imaging wire immediately before each pullback is mandatory

Careful evaluation of acquired pullback before finalizing procedure:

- Blood in catheter?
- Insufficiently flushed vessel?
- Target area acquired?
- SB ostium visible? (excess wire shadow?)

REPEAT PULLBACK IF QUALITY IS INSUFFICIENT

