**2.3 Treatment step-by-step**

Before arrival et cath lab, loading with acetylic salisylic acid and one of the antiplatelet agents clopigrogel/pragusgrel/ticagrelor is mandatory. Heparin or bivalirudin at start of procedure. After angiography and confirmation of presence of thrombus GpIIb/IIIa inhibitors are administered at operators discretion.

After thrombus aspiration with TIMI flow 2 or more the patient will be asked to participate in the study. Oral consent witnessed by staff non-affiliated with the study will be obtained.

OCT scan will be performed after 0.2 mg intracoronary nitroglycerine for sizing and lesion evaluation. The patient is then randomized into one of two arms in a 1:1 distribution:

1. Direct stenting with everolimus eluting stent
2. Direct stenting with bioresorbable stent

Direct stenting is the preferred method of implantation to keep procedure as short and simple as possible. Predilatation will not considered protocol violation if deemed necessary by operator. After stenting and post dilation at operator’s discretion, a second OCT will be performed. Any further post dilatation will be performed at operator’s discretion. A final OCT will be done if further postdilatation is performed. 0.2 mg intracoronary nitroglycerine is administered before each OCT scan.

Patient will be asked to sign an informed consent after the procedure (<24 hrs).

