**3.0 Data management and statistical analysis**

**3.1 Primary endpoint**

The primary endpoint in the two groups will be analyzed on patient level using paired t-test. A p-value considered indicating significance will be 5%.

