**3.2 Secondary endpoints and other variables**

Differences in categorical variables between the two groups will be analyzed using the chi-square test or Fisher´s exact test. Continuous variables will be analyzed using independent sample t-test and Mann-Whitney U-test, and time to event data will be analyzed using the Kaplan-Meier method and the log-rank test. OCT and angiographic parameters will be evaluated by Spearman correlation analysis. Binary logistic-regression analysis will be performed to identify independent predictors of difference in outcome. Pre and post PCI OCT of vessel size, lesion severity, lesion length. All p-values are two-sided. Level of significance is 5%. The analysis is performed on an intention to treat basis and by actual treatment.

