**3.3 Sample size calculation**

The Coronary Healing Score has not previously been validated in studies. The sample size calculation is therefore done using a Minimum flow Area (MinFA), the endpoint used in the TROFI trial, also investigating STEMI patients with OCT at follow up.

Following the assumptions of a Non-Inferiority design the sample size calculations of this study were based on pooled data of Cardialysis database from multiple trials in acute coronary syndrome where the MinFA was 4.95 + 1.39 mm2. The trial is powered for testing of noninferiority for the primary angiographic endpoint (Minimum Flow Area). In order to be able to reject the null hypothesis that standard treatment with DES produces a MinFA of at least 0.72mm2 better then the experimentaly treated group (BVS) requires a sample size of 54 patients per treatment group (alpha = 0.05 , power = 0.85 , predefined noninferiority margin = 0.72 mm2).

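### The primary comparison is fixed as an unadjusted (and wrongly paired) t-test although an OCT for sizing is planned before randomisation, so precision may be lost

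*Protocol*

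**What the plan says.** - **Primary analysis (Protocol 3.1).** "The primary endpoint in the two groups will be analyzed on patient level using paired t-test". No covariate is named.
- **Primary endpoint (2.2.6).** The Coronary Stent Healing Index is a summed points score for strut coverage, malapposition, neointima or diameter stenosis, and extra-stent lumen increase. No SD, expected value or margin is given for it.
- **Baseline imaging (2.3).** "OCT scan will be performed after 0.2 mg intracoronary nitroglycerine for sizing and lesion evaluation", and the next sentence reads "The patient is then randomized into one of two arms in a 1:1 distribution". The scan therefore precedes allocation in both arms.
- **Where the baseline OCT variables appear (3.2).** "Pre and post PCI OCT of vessel size, lesion severity, lesion length" is a fragment that follows the logistic regression for predictors, in the section on secondary endpoints. It is not tied to the primary comparison, and it mixes values from before and after the intervention.
- **Sample size (3.3).** It is computed on MinFA because the healing score is unvalidated: SD 1.39 mm2, "alpha = 0.05 , power = 0.85 , predefined noninferiority margin = 0.72 mm2", 54 per group. Section 2.2 plans 120 patients.
- **Timing of the pre-PCI scan.** Section 2.2.12 has "Pre PCI: (after predilatation) OCT imaging catheters will be inserted". Section 2.3 mentions predilatation only after the randomisation step and as optional: "Predilatation will not considered protocol violation if deemed necessary by operator".

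**The concern.** In a trial of this size, between-patient variation in vessel size can be a material part of the error term for a lumen-based outcome. An unadjusted test leaves that variation in, and it offers no protection against chance imbalance in vessel size between the arms. Adjusting for a value fixed before allocation removes whatever part of the variation the covariate explains, without introducing bias.

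The protocol plans to collect such a value and lists it as a variable of interest, but leaves it out of the comparison that decides the trial. Section 3.1 commits to a named test, so this is a choice the protocol has made and not merely a detail left open. The sentence has to be rewritten anyway: nothing pairs a patient in one arm with a patient in the other. Section 3.2 already uses independent-samples tests for other continuous variables.

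At stake is the width of the confidence interval behind the non-inferiority conclusion.

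**Working it through.** **Inputs from the protocol.** SD 1.39 mm2, margin 0.72 mm2, alpha 0.05, power 0.85, 54 per group (3.3); 120 patients, that is 60 per arm at 1:1 (2.2, 2.3). The true difference is taken as 0.

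**Assumed input.** r, the correlation between the baseline covariate and the 12-month outcome. The protocol gives none, so a range is shown.

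**Step 1: reproduce the stated size.** n per arm = 2 × [(z for alpha + z for power) × SD / margin]².
- One-sided 5%: 2 × [(1.645 + 1.036) × 1.39 / 0.72]² = 53.6, rounded up to 54. This matches. A t-based calculation gives 55.
- One-sided 2.5%: 2 × [(1.960 + 1.036) × 1.39 / 0.72]² = 66.9, rounded up to 67. This does not match.

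The stated 54 therefore rests on one-sided 5% and no covariate adjustment.

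**Step 2: effect of adjustment on MinFA.** The residual SD becomes 1.39 × √(1 − r²), so SE = 1.39 × √(1 − r²) × √(2/54). With r = 0, SE = 1.39 × 0.1925 = 0.268 mm2. Power is from the noncentral t distribution with noncentrality 0.72/SE and 106 degrees of freedom, or 105 with one covariate. The equivalent unadjusted size is 54/(1 − r²).

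| Assumed r | SE (mm2) | CI narrower by | Power, one-sided 5% | Power, one-sided 2.5% | Equivalent n per arm |
|---|---|---|---|---|---|
| 0 (unadjusted) | 0.268 | – | 84.8% | 76.0% | 54 |
| 0.2 | 0.262 | 2.0% | 86.1% | 77.7% | 56 |
| 0.3 | 0.255 | 4.6% | 87.7% | 79.8% | 59 |
| 0.5 | 0.232 | 13.4% | 92.5% | 86.9% | 72 |
| 0.7 | 0.191 | 28.6% | 98.2% | 96.2% | 106 |

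The 2.5% column is shown because section 3.2 calls all p-values two-sided at 5%. The normal approximation gives values within one percentage point of these (85.2% unadjusted at one-sided 5%).

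**Step 3: cost if the covariate is useless.** With r = 0 and one degree of freedom spent, power at one-sided 5% goes from 84.84% to 84.83%.

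**Step 4: comparison with the planned reserve.** 120 − 2 × 54 = 12 patients, or 10% of enrolment. With all 60 per arm evaluable and no adjustment, power is about 88.0% at one-sided 5%, close to the adjusted figure at 54 per arm with r = 0.3.

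**Step 5: the actual primary endpoint.** With no SD, margin or correlation for the Coronary Stent Healing Index, Steps 1 to 4 cannot be repeated for it.

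**The case against.** The strongest reply is that an unadjusted comparison of randomised groups is valid, that covariate adjustment is often settled in an SAP (not shown here), and that every figure above is for MinFA and not for the endpoint that section 3.1 analyses. Most of the index scores strut coverage and apposition, and nothing in the protocol says that baseline vessel size predicts these.

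Much of that stands. This is an efficiency point, not an invalidity, and the benefit for the index is unknown. It does not remove the point, because section 3.1 names a specific test that has to be corrected anyway, and adding a covariate in that correction costs almost nothing.

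A reader might infer more than the protocol supports in four ways:
- **That precision is certainly lost.** This needs a correlation that the protocol does not give. At r of 0.2 or less the gain is only about 1 percentage point at one-sided 5% (under 2 at one-sided 2.5%), even for MinFA.
- **That vessel size is known for every patient before randomisation.** Section 2.3 plans this. Section 2.2.12 describes the pre-PCI scan as following predilatation and foresees pullbacks of insufficient quality.
- **That the trial has no slack.** The planned 120 exceeds the required 108, although missing 12-month OCT may use up the difference.
- **That the adjusted limit for the index can be set against the margin.** The only margin, 0.72 mm2, is on MinFA.

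**Conclusion.** The point holds as a low-cost improvement. Section 3.1 fixes an unadjusted comparison with a test that does not fit the design, while section 2.3 plans a usable baseline measurement before allocation. Precision may be lost.

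For MinFA at one-sided 5%, the gain in power runs from about 1 percentage point (r = 0.2) through 3 (r = 0.3) and 8 (r = 0.5) to 13 (r = 0.7). This assumes SD 1.39 mm2, 54 evaluable per arm, a true difference of 0 and a linear relation with the covariate. For the Coronary Stent Healing Index the gain cannot be stated and could be small; the price is one degree of freedom. The conclusion also depends on the baseline scan really preceding randomisation, on which sections 2.2.12 and 2.3 do not clearly agree.

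**What to change.** In section 3.1:

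1. Replace the paired t-test with a prespecified linear model (ANCOVA) of the 12-month endpoint on treatment arm and pre-randomisation OCT vessel size, optionally with lesion length. Report the adjusted difference with its confidence interval.
2. Report the unadjusted independent-groups comparison as sensitivity analysis.
3. State a simple rule for an unreadable baseline OCT, for example replacing the covariate by its overall mean, so that no patient is dropped for that reason.
4. State that post-PCI OCT values are not covariates in the treatment comparison, since treatment affects them.
5. Compare the adjusted confidence limit with 0.72 mm2 for MinFA only. A non-inferiority claim on the healing index needs a margin of its own, which the protocol does not state.

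Reconcile sections 2.2.12 and 2.3 on when the pre-PCI OCT is taken relative to predilatation and randomisation, so that the covariate is clearly pre-randomisation.

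The cost is a few sentences, with no new data, patients or procedures, and one degree of freedom per covariate.

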**Rationale**

The pathological analysis will be compared to pre-,post- PCI and follow-up OCT readings to establish if composition, size and age predicts residual thrombus pre PCI as measured stent result after PCI and primary and primary endpoint at follow-up as measured by OCT. These results will be published in a separate substudy paper.

- 1. **Study goals and objectives**

Study goal is to compare the performance of the Absorb bioresorbable scaffold with a metallic drug eltuting stent in the STEMI patient.

Hypothesis is that a bioresorbable vascular scaffold (BVS) is non-inferior to standard of care, eg. direct stenting with metallic DES, using direct stenting after thrombus aspiration.

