**2.0 Study design**

The study is a prospective, randomized, controlled, non-blinded, multicenter study comparing metallic drug eluting stent with bioresorbable scaffold in STEMI patients. Primary endpoint Coronary Stent Healing Index, see 2.2.6 for definition.

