**6 Expected outcome of the study**

We expect to find no difference in the minimal flow area, or the secondary endpoints of MACE and stent failure.

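### The hypothesis is non-inferiority, but section 3.1 tests the Coronary Stent Healing Index only by a t-test at 5%, with no margin; the only margin in the protocol belongs to Minimum Flow Area

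*Protocol*

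**What the plan says.** - **Hypothesis** (section 1, study goals and objectives): "Hypothesis is that a bioresorbable vascular scaffold (BVS) is non-inferior to standard of care".
- **Primary endpoint** (section 2.0): "Primary endpoint Coronary Stent Healing Index, see 2.2.6 for definition". Section 2.2.6 builds the index by adding points for uncovered struts, malapposition, neointimal thickness or stenosis, and lumen increase outside the stent, so more points mean worse healing.
- **Primary analysis** (section 3.1): "The primary endpoint in the two groups will be analyzed on patient level using paired t-test". The only criterion attached is "A p-value considered indicating significance will be 5" per cent.
- **Sidedness** (section 3.2, on secondary endpoints and other variables): "All p-values are two-sided". Section 3.1 does not state it.
- **Sample size** (section 3.3): "The Coronary Healing Score has not previously been validated in studies", so the calculation uses another variable: "The trial is powered for testing of noninferiority for the primary angiographic endpoint (Minimum Flow Area"). The null there is that DES gives a MinFA better by at least 0.72 mm2. The inputs are SD 1.39 mm2, alpha 0.05 and power 0.85, giving 54 per group.
- **Expected outcome** (section 6): "We expect to find no difference in the minimal flow area, or the secondary endpoints of MACE and stent failure".

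**The concern.** A non-inferiority claim needs a margin on the scale of the endpoint, and a rule that rejects inferiority by that margin or more. Section 3.1 has neither. A t-test at 5% without a stated margin is ordinarily a test of no difference. A small p-value then shows a difference, and a large one leaves the question open.

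The margin in section 3.3 cannot be borrowed for the index. It is in mm2 with larger values better, while the index is in points with larger values worse.

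What is at stake is the trial's main conclusion. If BVS is about as good as DES, which is the case a non-inferiority trial is designed for, the stated analysis has no route to the intended claim. If a non-significant p-value were taken as that claim, the error rate would be well above the one planned, and it would rise as evaluable OCT follow-up is lost.

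**Working it through.** **1. Reproduce the plan's figure.** Inputs from section 3.3: margin 0.72 mm2, SD 1.39 mm2, power 0.85, alpha 0.05. Assume a true difference of 0.

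n per arm = 2 x SD^2 x (z_alpha + z_power)^2 / margin^2

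- One-sided 5%: 2 x 1.9321 x (1.645 + 1.036)^2 / 0.5184 = 53.6, so **54**. This matches.
- One-sided 2.5%: 2 x 1.9321 x (1.960 + 1.036)^2 / 0.5184 = 66.9, so 67. This does not match.

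The stated size is therefore a one-sided 5% non-inferiority calculation on MinFA. Its planned chance of declaring non-inferiority when BVS is worse by exactly the margin is 5%.

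**2. Set the sections side by side.**

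| Element | Healing index | MinFA |
|---|---|---|
| Called primary endpoint | 2.0, 2.2.6, 2.2.8 | only as primary angiographic endpoint, 3.3 |
| Named in the secondary lists (2.2.7) | no | no |
| SD | none | 1.39 mm2 |
| Margin and non-inferiority null | none | 0.72 mm2, in 3.3 |
| Primary analysis rule | t-test at 5%, in 3.1 | none |

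The endpoint with an analysis rule has no margin, and the variable with a margin has no analysis rule.

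**3. What the rule in 3.1 can show, read as a difference test.**

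- Significant, BVS better: non-inferiority follows for any positive margin.
- Significant, BVS worse: a difference is shown. Whether it exceeds an acceptable amount cannot be said without a margin.
- Not significant: nothing follows about non-inferiority.

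**4. Illustration of the risk, on MinFA inputs.** Assumptions: two independent groups (allocation is 1:1 and no pairing of patients is defined), a two-sided 5% test as in 3.2, SD 1.39, and a true BVS deficit of 0.72 mm2 (0.72 / 1.39 = 0.518 SD).

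- Standard error = 1.39 x sqrt(2/n): 0.268 mm2 at 54 per arm and 0.254 at 60.
- Noncentrality = 0.72 / standard error: 2.69 at 54 and 2.84 at 60.
- P(not significant), noncentral t: **24.0%** at 54, **19.7%** at 60, 31.9% at 45. The normal approximation gives 23% at 54 and 19% at 60.

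Against the planned 5%, that is 24.0 / 5 = 4.8 times at 54 per arm and 19.7 / 5 = 3.9 times at 60.

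**5. The same contrast for observed results (54 per arm, normal approximation).** The 95% half-width is 1.96 x 0.2675 = 0.52 mm2, and the 90% half-width is 1.645 x 0.2675 = 0.44 mm2. A difference test is non-significant for an observed deficit up to 0.52 mm2. Non-inferiority at one-sided 5% needs an observed deficit below 0.72 - 0.44 = 0.28 mm2. An observed deficit between 0.28 and 0.52 mm2 is thus non-significant and yet fails to show non-inferiority.

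**6. The index.** With no SD or margin in the protocol, neither an error rate nor a power can be computed for it.

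**The case against.** **Section 3.3 does state a proper non-inferiority null.** It does, and a t-test can be run against a shifted null. But that null concerns MinFA. Section 3.1 concerns the index, gives no shift, and does not refer to 3.3. The fair statement is that the test in 3.3 was never carried into the analysis section and the index has no margin.

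**A reader might infer that no result could establish non-inferiority.** That goes too far. A significant result in favour of BVS would establish it.

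**A reader might infer that the sponsor intends to treat non-significance as non-inferiority, citing section 6.** The protocol does not say this. Section 6 states an expectation, not a decision rule, and it does not mention the index. Expecting no difference is also the usual assumption behind a non-inferiority sample size, and 54 per group reproduces with a true difference of 0. The misreading is a risk, and section 6 needs no rewording on this account.

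**The 24% is borrowed.** This stands. It uses MinFA's SD and margin, and its two-sidedness comes from 3.2. It cannot be transferred to the index: nothing in the protocol marks a deficit of 0.52 SD on the index as unacceptable.

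**The SAP could settle it.** An SAP can add detail, but section 3.1 already fixes a rule, and that rule does not test the stated hypothesis.

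**Conclusion.** The plan is wrong as written. The hypothesis is non-inferiority, the primary analysis is a t-test at 5% with no margin, and the only margin and non-inferiority null belong to a different variable. This rests on the text alone. As written, non-inferiority can be supported on the primary endpoint only if BVS is significantly better.

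The size of the risk is illustrative: 24% at 54 per arm and 20% at 60, against a planned 5%. It assumes MinFA inputs, two independent groups, a two-sided 5% test, a true deficit equal to the margin, and that a non-significant result is misread. The point must be settled before the results are analysed, because it decides whether the trial's main question can be answered.

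**What to change.** **Preferred.** Rewrite section 3.1 so that the non-inferiority claim rests on MinFA. Declare BVS non-inferior only if the lower limit of the two-sided 90% confidence interval for BVS minus DES lies above -0.72 mm2. This is one-sided 5%, the level at which the stated 54 per group reproduces. Report the healing index as a between-group difference with a 95% confidence interval and no non-inferiority claim. Sections 2.0, 2.2.6 and 2.2.8 must then agree on which endpoint carries the claim, and MinFA must be listed as an endpoint. The cost is an amendment in wording, approved by the steering committee, with no added patients.

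**If one-sided 2.5% is chosen instead.** Restate MinFA power: about 76% at 54 per arm and 80% at 60 (noncentral t). Power of 85% would need 67 per arm by the normal approximation, or 134 in all against the 120 planned.

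**If the index is to carry the claim.** Fix and justify a margin on the index scale before any 12-month OCT is scored, require the upper confidence limit for BVS minus DES to lie below it, and restate the power. The cost depends on the margin. For assumed margins at one-sided 5%, 85% power and no true difference, 0.6 SD needs 40 per arm, 0.5 SD needs 58, 0.4 SD needs 90 and 0.3 SD needs 160, against 60 per arm planned.

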**3.2 Secondary endpoints and other variables**

Differences in categorical variables between the two groups will be analyzed using the chi-square test or Fisher´s exact test. Continuous variables will be analyzed using independent sample t-test and Mann-Whitney U-test, and time to event data will be analyzed using the Kaplan-Meier method and the log-rank test. OCT and angiographic parameters will be evaluated by Spearman correlation analysis. Binary logistic-regression analysis will be performed to identify independent predictors of difference in outcome. Pre and post PCI OCT of vessel size, lesion severity, lesion length. All p-values are two-sided. Level of significance is 5%. The analysis is performed on an intention to treat basis and by actual treatment.

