**2.2 Patients**

We propose to include 120 patients presenting with STEMI with less than 12 hrs. history.

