**2.2.4 Procedural contraindications:**

1. Heavy calcification, tortuous vessel or large side branch (> 2,5 mm) at culprit lesion.
2. TIMI 0-1 flow after aspiration
3. Unable to advance thrombus aspiration catheter

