**2.2.7.2**

Angiographic endpoints

1.TIMI flow pre and post PCI,

2.Blush grade

3.Thrombus burden

4. Angiographic complications

5. Contrast use

6. Procedure time

7. Radiation skin dose

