**2.2.7.3**

Clinical endpoints

Index admission:

1.total death

2. Cardiac death

3. Non-index procedure myocardial infarction

4. Stent thrombosis (definite and probable)

5. TLR and TVR

6. non-TVR

Follow up:

1. Total death

2. Cardiac death

3. Non-index procedure myocardial infarction

4. Stent thrombosis (definite and probarble)

5. TLR and TVR

6. non-TVR

7. CCS angina class

8. Vascular cerebral events

9. Admissions for congestive heart failure or arrhythmia

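### Section 3.2 as written sends ordered grades (blush, CCS class, and post-PCI TIMI flow if more than two grades occur) to tests that ignore order: valid, but less powerful than the rank test it already names

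*Protocol*

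**What the plan says.** Section 3.2 of the protocol gives one rule per type of variable for comparing the arms. For the first type, "Differences in categorical variables between the two groups will be analyzed using the chi-square test" or Fisher's exact test. For the second, "Continuous variables will be analyzed using independent sample t-test and Mann-Whitney U-test". Time-to-event data have their own methods. On error control it says "All p-values are two-sided", at the 5% level. No trend, rank or ordinal method is named for graded scales. The Spearman analysis in the same section correlates OCT with angiographic parameters and does not compare arms.

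Three listed secondary endpoints are ordered grades: TIMI flow ("1.TIMI flow pre and post PCI") and blush grade in 2.2.7.2, and "7. CCS angina class" at follow-up in 2.2.7.3. The protocol does not say outright which rule covers them.

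**The concern.** The grades are neither continuous nor time-to-event, which leaves the chi-square/Fisher rule. With k grades, that test asks whether the two distributions differ in any way and spreads the evidence over k − 1 degrees of freedom. The question of interest is narrower: does the scaffold give worse blush, worse flow or more angina than the metallic stent? A test that uses the order puts the evidence for such a shift into one degree of freedom.

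At stake is sensitivity. In a trial of about 60 patients per arm, a real shift towards worse grades is easier to miss with the order-blind test. For a scale with several grades, that test's result also carries no direction.

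**Working it through.** **Inputs from the protocol.** The total is 120 (2.2: "We propose to include 120 patients presenting with STEMI with less than 12 hrs. history"), randomized 1:1 (2.3), so 120/2 = 60 per arm. Tests are two-sided at 5% (3.2).

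**The plan's own figure.** The only sample-size figure concerns minimum flow area (3.3): n = 2 × 1.39² × (1.645 + 1.036)² / 0.72² = 53.6, so 54 per group. It reproduces with a one-sided 5% alpha. It says nothing about the graded endpoints, for which no power is claimed.

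**Check 1: analytic.** Assume the whole effect lies along the order. A 1-df test has 80% power when the noncentrality is λ = (1.960 + 0.842)² ≈ 7.85. The power of a chi-square test with the same λ and more degrees of freedom is:

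| Grades | df | Critical value | Power | Loss against 80% |
|---|---|---|---|---|
| 3 | 2 | 5.99 | 71% | 9 points |
| 4 | 3 | 7.81 | 64% | 16 points |
| 5 | 4 | 9.49 | 60% | 20 points |

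Over 1-df powers from 50% to 90%, the loss is 6 to 10, 12 to 17 and 16 to 22 points respectively.

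**Check 2: simulation.** Everything about the grades is assumed here: the number of levels, the control distribution and the effect. The shift is proportional odds: at every cut-point, the odds of the worse side are multiplied by the odds ratio (OR). The comparison is Pearson's Σ(O − E)²/E, on one df fewer than the grades observed, against the tie-corrected Mann-Whitney test. Examples at 60 per arm, each with a shift towards worse grades:

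| Assumed control distribution | OR | Chi-square | Mann-Whitney | Gap |
|---|---|---|---|---|
| Three grades, 20/30/50% | 2.5 | 67% | 77% | 10 |
| Blush-like, four grades, 5/15/35/45% | 2 | 38% | 54% | 16 |
| CCS-like, four grades, 60/25/10/5% | 2.5 | 58% | 75% | 17 |
| CCS-like, five grades, 40/25/20/10/5% | 2.5 | 58% | 79% | 21 |

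For odds ratios of 2 to 3 over the distributions tried, the gap was about 6 to 11 points with three grades, typically 12 to 18 with four, and up to about 24 with five. It closes when both tests approach full power: the blush-like case at OR 4 gives 94% against 98%. At 54 per arm the pattern is the same.

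**Check 3: TIMI flow.** "TIMI 0-1 flow after aspiration" is a procedural contraindication (2.2.4), and consent and randomization follow aspiration with flow of grade 2 or more (2.3). If only grades 2 and 3 occur after PCI, the table is 2 × 2, the two tests are practically the same, and the gap is 0. If all four grades occur with 90% in grade 3 (1/2/7/90%), OR 2.5 at 54 per arm gives 22% against 39%. Part of that gap is conservatism from sparse cells: with no effect, chi-square rejects only 2.5% of the time there. Pre-PCI TIMI flow is measured before the randomized device is placed, so power for a treatment effect does not apply to it.

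**Check 4: what the order-based test gives up.** For non-monotone differences the ranking reverses. With 25/25/25/25% against 10/40/40/10%, chi-square has 86% power and Mann-Whitney about 6%. Over three such examples chi-square had 72% to 86% and Mann-Whitney about 5%.

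**The case against.** The strongest reply is that section 3.2 is a generic rule, never assigns these grades to chi-square by name, and already lists the Mann-Whitney test; a statistical analysis plan that is not shown may settle the matter. It is true that the assignment is an inference. But the protocol is not silent here: it states a rule by variable type, ties Mann-Whitney to continuous variables, and leaves only one place for a graded class. An analysis plan could refine this, yet the protocol sentence would still point the other way.

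A second reply is that chi-square and Fisher are valid on graded data and that no power was promised for these endpoints. That stands in full, and it limits the point to efficiency.

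Third, where cells are sparse Fisher's exact test would normally be used, and only Pearson's test was simulated. That also stands. Fisher's test ignores order too, so the reason for the loss remains, but its size with Fisher is not established here.

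A reader might also infer that the order-blind test has no merit. Check 4 shows that it does, although patterns of that kind matter little when the question is whether one device is worse.

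**Conclusion.** The point holds as a minor, inexpensive improvement. Under the plain reading of 3.2, blush grade and CCS class, and post-PCI TIMI flow if more than two grades occur, would be compared by tests that discard their order. With 60 per arm, proportional odds ratios of 2 to 3 and assumed distributions, the cost runs from 0 points (two grades) to about 24 points (five CCS levels), typically 12 to 18 with four grades.

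Three stronger readings are tempting, and the protocol does not support them:

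- **A single fixed loss for this trial.** The protocol gives no grade distributions or effect sizes, so only a range under stated assumptions can be given.
- **TIMI flow as the leading example.** It may lose nothing. Blush grade and CCS class carry the point.
- **A threat to the trial's conclusion.** The expectation of no difference in section 6 names minimal flow area, MACE and stent failure, not these grades. The primary analysis is unaffected.

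**What to change.** In section 3.2, limit the chi-square/Fisher rule to binary and nominal variables and add one sentence: ordinal grades (blush grade, CCS angina class, post-PCI TIMI flow) are compared between arms with the Mann-Whitney U-test with tie correction. Optionally, add a common odds ratio from a proportional-odds model with its 95% confidence interval, which gives a direction and a size.

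This needs no new data, visits or patients, and the test is already in the plan. The price is little power for non-monotone differences. Tabulating the full grade distribution by arm would let a reader see such a pattern. The sentence should be fixed before outcomes are compared by arm.
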